## Interventions

### Comic book

The original comic book titled “Let’s Talk About It” is a 28-page Graphic Guide to Mental Health that was originally co-created by the Cartoon Studies Lab for the Ohio State Department of Health (USA), specifically designed for middle and high school students (https://www.cartoonstudies.org/css-studio/cartooningprojects/mentalhealth/). As a light-touch intervention, we chose two pages from the comic book that specifically highlight the two most prevalent mental disorders in this population: Anxiety and Depression (see Fig. 2). These pages primarily convey information about mental health, understanding mental disorders, guidance on seeking help, and addressing stigma through storytelling with an illustrated cast of rabbit characters. Each page briefly explains how biological processes in the brain result in anxiety and depression and how a disorder differs from feeling stressed or feeling blue. It also covers the Diagnostic and Statistical Manual of Mental Disorders, Fifth Edition (DSM-5) [29] based on symptomology for each disorder. Notably, we adapted the rabbit character by using a darker shade of brown fur to reflect a representative skin color that is prevalent within the cultural context. Also, we collaborated closely with the local mental health expert practicing in Burkina Faso, to translate and validate the English text into French, ensuring it was culturally sensitive and appropriate. Furthermore, we integrated local information platforms at the bottom of the page to provide participants with additional resources for further learning.

**Fig. 2 Fig2:**
[figure not shown]
Comic book as a light-touch intervention

### Flyer

The flyer intervention is designed to resemble the commonly used health information material in public health initiatives. The flyer contains text identical to that of the comic book. However, where text within illustrations could be confusing without accompanying visuals, we adjusted the wording slightly to maintain clarity. For example, in the comic book's text accompanying the first picture for Anxiety states: “Anxiety is an alarm from our brain’s fight, flight or freeze response. Hide. Fight. Run,” which may not fully convey its meaning without the illustration. The flyer version reads: “Anxiety is an alarm from our brain’s fight, flight or freeze response. It can look like fighting, freezing, or running away.” (See Fig. 3). This adaptation ensures that the information remains accessible and understandable without accompanying visuals, maintaining the goal of the flyer as an educational tool while nevertheless remaining very close to the comic book text.

**Fig. 3 Fig3:**
[figure not shown]
The flyer intervention

## Outcome measures

Our primary outcome will be the sum score on a revised version of a Universal Mental Health Literacy Scale for Adolescents (UMHL-A) [30], measured both before and after the intervention in wave 1 and a year later in wave 2. This scale assesses mental health literacy across domains such as mental health knowledge, mental disorder knowledge, help-seeking behavior, and stigma. The revised UMHL-A consists of 10 items, each rated on a 5-point Likert scale (1–5 points), yielding a total score ranging from of 10 to 50. Higher scores indicate a greater level of mental health literacy. Our secondary outcomes will include the total scores on the 2-item Patient Health Questionnaire (PHQ-2) [31, 32], the 2-item Generalized Anxiety Disorder (GAD-2) [32, 33], and the 2-item Intentions to Cope scale [34], all measured post-intervention.

Outcome assessment will happen as part of waves 1 and 2 of the DASH cohort study; as part of the DASH cohort study, an attempt will be made to identify and follow-up all participants from wave 1 in wave 2. Outcomes will be assessed during the survey interview conducted by a data collector. All data collectors will be trained in administering the full survey, which should ensure outcomes are collected for all participants. All scales used in our study will be translated into French and reviewed by local mental health experts for cultural sensitivity. To assess reliability, we will calculate Cronbach’s alpha within our sample [35].

First level of data entry and storage will be on a tablet before forms can be uploaded online. At this level only data collectors involved in the interview and/or data manager will have access to the data collected. Data collectors are responsible for privacy and confidentiality of the data on the device. Second level of data storage will be on the online server. Application developers will be responsible for setting up the server for online data storage. Server setup will include password protected access and different levels of access to ensure only authorized individuals can access the data online and only access their allowable sections of the application and/or data sources.

Data cleaning will first be done on the tablet before the forms are uploaded online. Data collectors will be responsible for checking sections of the questionnaire for errors. The second level of data cleaning will be done by data managers after downloading the data from the online server. At this step, data will be checked for any duplicates (using household identifiers) and any failed logical checks. Any data errors resulting from how the questions are setup and/or asked will be communicated to program managers immediately.

## Data analysis

We will assess participants’ sociodemographic characteristics, including age, gender, education levels, ethnicity, religion, household characteristics, and their parents’ highest level of education and occupation with outcome measures. To assess the effectiveness of an intervention on mental health literacy (MHL), we will build a multiple regression model. We will also assess each sub-scale component of MHL (knowledge about mental health, knowledge about mental health, help-seeking, and stigma). Here, the independent variable is “3 arms”, representing different intervention groups, and the outcome will be “MHL after the intervention.” We will control for baseline MHL scores by including them as a covariate, following the recommendation by Senn (2006) to adjust for potential baseline differences [36]. For the analysis, we will employ dummy coding for the three trial arms to compare each intervention arm against the control arm. In addition, covariates such as depressive and anxiety symptoms, intentions to cope, age, gender, and education levels will be included in the model. Secondary outcomes will be examined using three separate linear regression models, with the trial arm” treated as a factor and the control arm serving as the reference category for each secondary outcome. To ensure the validity of our multiple regression analysis, we will calculate variance inflation factor values to check for multicollinearity among the independent variables. We will conduct statistical analyses using *R version 4.1.0* (www.r-project.org).

The final cleaned, de-identified and locked dataset of the trial will be accessible by the DASH network partners. Public access to the data will be made available upon review of the request and approval by each institute’s Principal Investigators.

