**Discussion:**

We hypothesize that the comic book intervention and flyer intervention will prove more effective in improving mental health literacy than the control group. We further hypothesize that for younger adolescents (10–14), the comic book will be more effective at increasing mental health literacy than the flyer. Conversely, we hypothesize that the flyer will be more effective in increasing mental health literacy for older adolescents (15–24). Our study will provide evidence on novel interventions designed to enhance mental health literacy among adolescents and young adults in low-resource settings.

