This study aims to evaluate whether an illustrated comic book or a brochure-like flyer (text-only) that describes the mental disorders of anxiety and depression as well as information around help-seeking and coping, is more effective at increasing mental health literacy for certain age groups. We hypothesize that both the comic book and the flyer will increase mental health literacy for all ages compared to a control group that receives no intervention. However, we hypothesize that the comic book will be more effective in increasing mental health literacy with younger adolescents (ages 10–14) compared to older adolescents and youth (ages 15–24) due to the engaging nature of illustrations for young readers. The primary outcome will be mental health literacy and secondary outcomes will include anxiety, depression, and intentions to cope. We will also explore how the information in the comic book and flyer might impact anxiety and depression scores as previous studies have shown that at times, individuals are negatively impacted after consuming information about depression [25]. The primary and secondary outcomes will be assessed directly following the implementation of the intervention for the comic book and flyer groups.

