## Discussion

This study will contribute valuable information on light-touch interventions for improving mental health outcomes for adolescents and youth in LMICs. We will use an efficient, low cost, scalable, and validated intervention to enhance MHL among adolescents and youth in Burkina Faso. Our findings will add knowledge on the effectiveness of using a comic book to increase knowledge about mental health and mental disorders, facilitate help-seeking behaviors, reduce stigma, and thereby enhance overall MHL. In addition, we will determine if comic books are more effective for specific age groups of adolescents and youth compared to a text-only flyer. This work will advance Burkina Faso’s 2020–2024 Mental Health Strategic Plan and employ strategies suggested by the WHO Mental Health Action Plan 2013—2020. Increasing MHL has the potential to improve mental health outcomes as low levels of MHL have been linked to adverse mental health outcomes [37]. As randomized control trial studies on the effectiveness of comic books in impacting mental health literacy are few, this study will also add high quality research to future researchers who are considering this method of delivery.

Due to the nature of this light-touch intervention, its long-term effectiveness may be limited. In addition, the exposure to the light-touch intervention would benefit from repeated exposure over a period of time. By harnessing the potential of the comic book approach and incorporating lessons learned from this study, we aim to create a comprehensive comic intervention, including a digital format, in the future. Moreover, we will investigate the effect of our comic intervention on other countries part of the DASH study, including Ethiopia, Ghana, Nigeria, Uganda, South Africa, and Tanzania. Our study will provide valuable insights into innovative and engaging ways of communicating mental health information to adolescents and youth through NSHP delivery agents.

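### The stated literacy model has no comic-versus-flyer contrast and no arm-by-age term, so it does not test the age hypotheses, which are themselves worded in two non-equivalent ways

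*Protocol article*

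**What the plan says.** **Hypotheses.** The Abstract (Discussion paragraph) predicts that "for younger adolescents (10–14), the comic book will be more effective at increasing mental health literacy than the flyer" and, conversely, that "the flyer will be more effective in increasing mental health literacy for older adolescents", meaning ages 15–24. The Introduction predicts that "the comic book will be more effective in increasing mental health literacy with younger adolescents" than with those aged 15–24, and makes no claim that the flyer is superior in the older group. Both also expect each intervention to beat control.

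**Promised conclusion.** The main Discussion says "we will determine if comic books are more effective for specific age groups of adolescents and youth compared to a text-only flyer".

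**Analysis.** Under Data analysis: "To assess the effectiveness of an intervention on mental health literacy (MHL), we will build a multiple regression model". The outcome is literacy after the intervention, baseline literacy is a covariate, and "we will employ dummy coding for the three trial arms to compare each intervention arm against the control arm". Age is listed with gender, education and symptom scores as a further covariate. No product of arm and age, no age-stratified model and no comic-versus-flyer contrast is stated.

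**Age subgroups elsewhere.** The section on sample size and power divides the sample by nine for a subgroup analysis. Table 1 has an age sub-groups row with 223 per arm and detectable d of 0.32 (wave 1) and 0.34 (wave 2). Under Procedure, randomisation is stratified by three age categories.

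**The concern.** The article's aim is to learn whether comic or flyer works better for particular age groups. A regression with arm and age as separate main effects gives one comic effect and one flyer effect for everyone from 10 to 24. Their difference can be recovered from the fit, although it is not named, but it too is a single number for all ages. The fitted model therefore says nothing about whether that difference changes with age.

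Because the hypothesis is worded in two ways, the analyst could also decide after seeing the data which claim the results are held against. The two claims can receive different verdicts from the same data.

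**Working it through.** **1. What the stated model can estimate.** In symbols: post-score = b0 + b1·comic + b2·flyer + b3·baseline + b4·age + other covariates. The comic effect is b1 at every age, the flyer effect is b2 at every age, and comic minus flyer is b1 − b2 at every age. The Abstract needs comic minus flyer separately at 10–14 and at 15–24. The Introduction needs the comic effect at 10–14 minus the comic effect at 15–24. Neither quantity is in the model.

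**2. Are the two wordings equivalent?** Take illustrative effects against control in SD units: comic 0.3 (younger) and 0.2 (older), flyer 0.1 in both.
- Introduction: 0.3 > 0.2, so true.
- Abstract, younger half: 0.3 > 0.1, so true.
- Abstract, older half (flyer better): 0.1 > 0.2 is false.

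The converse also occurs. If the comic effect is equal in both age groups while the flyer falls below it in the younger and above it in the older, the Abstract is right and the Introduction wrong.

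**3. Reproducing Table 1.** Inputs from the sample size section: power 0.80, alpha = 1 − 0.95^(1/√h), 669 or 223 per arm, 10% attrition at wave 2. The value of h is not given and two-sided tests are assumed. With a two-sample t-test:
- Full arms, h = 6 (alpha 0.0207): 0.173 and 0.182, matching 0.17 and 0.18.
- Age sub-groups, h = 18 (alpha 0.0120): 0.319 and 0.336, matching 0.32 and 0.34.

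The sub-group row is a comparison of two arms inside one age group.

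**4. Detectable effect for the between-age contrast.** The 15–24 group pools two strata, so it has 2 × 223 = 446 per arm. In SD units,

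SE = √(2/223 + 2/446) = √(0.00897 + 0.00448) = 0.116.

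At wave 2, with 90% retained, SE = 0.116/√0.9 = 0.122. The MDE is (z for alpha + 0.842) × SE:

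| Two-sided alpha | Wave 1 | Wave 2 |
|---|---|---|
| 0.05 | 0.325 | 0.343 |
| 0.0207 (h = 6) | 0.366 | 0.386 |
| 0.0120 (h = 18) | 0.389 | 0.410 |

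The same figures hold for comic minus control, because the arms are equal in size. No gain from covariates is included. If baseline and outcome correlate at 0.5 (an assumption), multiply by √(1 − 0.25) = 0.87.

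The 0.05 row lies close to Table 1's 0.32 and 0.34, but this is a coincidence of different alphas. At the same alpha the contrast is √1.5 = 1.22 times harder to detect than a difference between two arms of 223: 0.325 against 0.265 at alpha 0.05. At a true between-age difference of 0.32, wave 1 power is about 0.79 at alpha 0.05 and 0.60 at alpha 0.012.

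**The case against.** The strongest reply is that the article already foresees age subgroups, sizes them in Table 1 and stratifies randomisation by age. It is also a condensed article without its SAP, and the form of a subgroup model is often left there. Moreover, the Abstract makes two within-age claims, which within-age comparisons of comic and flyer address directly; an interaction is strictly needed only for a between-age claim. The expectation that each intervention beats control is answered by the model as stated.

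Much of this stands. A reader might infer that the trial cannot test its age hypotheses at all. The documents do not support that: the limit lies in the stated model, not in the design. A reader might also take moderation to be the reason for stratifying; Procedure gives only balance of arms within age categories.

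The reply does not close the gap, however. The sample size section names no model or contrast and uses three age groups where the hypotheses use two. Separate subgroup tests would not test the Introduction's between-age claim. An SAP cannot settle which hypothesis is meant while the protocol carries two.

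One could also compute how often separate 5% tests (223 and 446 per arm) make exactly one age group significant when the true effect is the same in both. This is 53%, 46% and 27% at assumed d = 0.15, 0.20 and 0.25. Those totals should not be read as the rate of false support for the hypothesised advantage in the young. Split by direction, younger-only significance is 14%, 8.5% and 3%, and older-only is 39.5%, 37% and 24%, because the older group is larger. The plan does not state this procedure or a plain 5% level for it.

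**Conclusion.** The point holds for the analysis as stated. The literacy regression contains neither a comic-versus-flyer contrast nor an arm-by-age term, so it does not test the age hypotheses in the Abstract and Introduction or deliver the conclusion promised in the Discussion. The two hypothesis statements are not equivalent. This is a mismatch between stated parts of the plan, not detail left for later.

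The moderation contrast has a detectable effect of about d = 0.32 to 0.39 at wave 1 and 0.34 to 0.41 at wave 2. These figures assume two-sided testing, 80% power, equal arms and no covariate gain. The upper ends assume h = 18, which reproduces Table 1's sub-group row but is not stated in the article.

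**What to change.** 1. State one age hypothesis, in the same words, in the Abstract and the Introduction.
2. In Data analysis, add arm × age group (10–14 versus 15–24) to the literacy regression.
3. From that model, report comic minus flyer with a confidence interval within each age group. This addresses the Abstract's claims, including the reversal, which a single interaction test would not establish.
4. Name the between-age difference in comic minus flyer as the test of moderation. If the Introduction's wording is the one kept, use the between-age difference in comic minus control.
5. Show the three randomisation strata descriptively, and link the subgroup analysis in the sample size section to this model.
6. State the MDE of the moderation contrast and the h behind its alpha, separately from Table 1's within-age figure.

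The cost is wording only, since the data and strata already exist. The drawback is that the detectable effect to be declared is less favourable than Table 1's sub-group figure at the same alpha (0.39 against 0.32 at wave 1 with alpha 0.012).

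### The analysis names only comparisons with control and no arm-by-age term, so nothing in it tests the stated question of comic versus flyer by age group

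*Protocol article*

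**What the plan says.** **The question.** The Introduction asks which of the two formats "is more effective at increasing mental health literacy for certain age groups". For ages 10–14 the abstract hypothesizes that "the comic book will be more effective at increasing mental health literacy than the flyer", and it predicts the reverse for ages 15–24. The closing Discussion makes this a commitment: "we will determine if comic books are more effective for specific age groups of adolescents and youth compared to a text-only flyer". The abstract and the Introduction also hypothesize that each intervention beats the no-intervention control.

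**The analysis.** For the primary outcome, the Data analysis section says "we will employ dummy coding for the three trial arms to compare each intervention arm against the control arm". The secondary models follow the same pattern, with "the control arm serving as the reference category for each secondary outcome". Age appears in one place: "covariates such as depressive and anxiety symptoms, intentions to cope, age, gender, and education levels will be included in the model". The section names no comic-versus-flyer contrast, no arm-by-age term and no age-stratified model.

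**The sizing.** Table 1 has a row for age subgroups (223 versus 223), but it does not say which arms are compared, and the Data analysis section describes no subgroup analysis.

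**The concern.** The named contrasts answer one family of hypotheses, each intervention against control, and leave the other without a test. The omitted family carries the comparison of formats. The Interventions section says the flyer's text is nearly the same as the comic's, so comic minus flyer is the contrast that isolates the illustrations.

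Two things follow if the section is carried out as written. First, a reader who wants the head-to-head answer has only two coefficients against a shared control, and setting their p-values side by side is not a test of their difference. Second, with age as a main effect only, the model assumes the same arm effect at every age, while the hypotheses say the effect changes direction. Any head-to-head or age-specific contrast added after the data are seen would be post hoc and would have no stated place in the multiplicity rule.

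**Working it through.** **Inputs** (Sample size and power considerations, and Table 1): N = 2,007, so 669 per arm and 223 per arm in each of three age categories; power 0.80; 10% attrition at wave 2; alpha = 1 − 0.95^(1/√h), with h based on the numbers of arms and outcomes but not stated. Ages 15–24 combine two categories, so 2 × 223 = 446 per arm. Assumed: two-sided tests, SD = 1, no precision gain from baseline adjustment.

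**Step 1. Reproduce Table 1.** MDE = (z[1−alpha/2] + 0.8416) × √(2/n).
- h = 6: alpha = 0.0207 and the multiplier is 2.3130 + 0.8416 = 3.1546. With n = 669, MDE = 3.1546 × 0.0547 = 0.172. With n = 602.1 (wave 2), MDE = 0.182. Table 1 gives 0.17 and 0.18.
- h = 18 (6 × 3 age groups): alpha = 0.0120 and the multiplier is 3.3533. With n = 223, MDE = 0.318. With n = 200.7, MDE = 0.335 (0.319 and 0.336 with the noncentral t). Table 1 gives 0.32 and 0.34.
- Unadjusted alpha 0.05 gives 0.153 and 0.162 for the full sample, and 0.266 and 0.280 for the subgroups (noncentral t). These do not match.

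Table 1 is therefore reproducible, with h inferred as about 6 for the full sample and about 18 for the subgroups.

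**Step 2. MDEs for the question as stated** (wave 1, normal approximation). The interaction is the difference between the two age groups in comic minus flyer, so its standard error is √(2/223 + 2/446) = 0.116.

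| Contrast | n per arm | h = 6 | h = 18 | h = 27 |
|---|---|---|---|---|
| Comic − flyer, pooled | 669 | 0.172 | 0.183 | 0.187 |
| Comic − flyer, 10–14 | 223 | 0.299 | 0.318 | 0.324 |
| Comic − flyer, 15–24 | 446 | 0.211 | 0.225 | 0.229 |
| Interaction, 10–14 vs 15–24 | 223 and 446 | 0.366 | 0.389 | 0.397 |

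At wave 2 each figure is divided by √0.9, which makes it about 5% larger.

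The pooled head-to-head contrast has the same n, and so the same MDE, as each contrast with control. The gap is in the named analysis, not in the sample size for that pairwise comparison.

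**Step 3. Why a pooled contrast is not enough.** The two age groups enter in the ratio 1:2. If comic minus flyer were +0.32 SD at 10–14 and −0.16 SD at 15–24, the pooled value would be (0.32 − 2 × 0.16)/3 = 0. The pattern the authors predict could vanish in the pooled estimate.

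**Step 4. Reading two control contrasts side by side.** Suppose comic and flyer are equally effective. The two test statistics share the control arm and have correlation 0.5. If both effects sit exactly at the MDE (80% power each), P(both significant) = 0.687, so exactly one is significant in 2 × (0.80 − 0.687) = 0.226 of trials. At the inferred h = 6 this falls to about 12% at d = 0.20 and 0.1% at d = 0.30.

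**The case against.** Several points on the other side have force.

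- *The coding blocks nothing.* This stands. A reader might infer that control-reference coding makes the comparison impossible. It does not: comic minus flyer, with its standard error, comes from the same fit through the coefficient covariance. The defect is that the contrast is not named.
- *The control comparisons are themselves hypothesized.* This also stands. A reader might conclude that the plan misses the purpose of the trial altogether, but it correctly tests that each intervention beats control, and those contrasts should stay.
- *An unseen analysis plan may list the contrasts.* This would settle the matter if the section were silent. It is not silent: it says which comparisons the coding is for and how age enters, and those choices do not match the stated question.
- *About 23% of trials would mislead.* A reader might take the 0.226 in the working as an expected error rate. It holds only if both effects lie exactly at the MDE and investigators read discordant significance as superiority, which the article never says they will do. The article expects medium to large effects, where the figure is far smaller. It is an illustration only.
- *The secondary outcomes need the same contrast.* The documents do not support this. The comic-versus-flyer hypotheses concern mental health literacy only. For anxiety and depression the Introduction wants to explore whether the information itself affects scores, and control is a natural reference for that.

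**Conclusion.** The point holds. No analysis named in the Data analysis section tests whether comic or flyer is better for mental health literacy by age group, although the abstract hypothesizes it, the Introduction asks it and the Discussion promises an answer. This is a mismatch between the question and the analysis that the article fixes, and it can be repaired without any change to the design: randomization is already stratified by age and the arms are already sized.

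The size of the problem is best given by what the trial can detect on this question: about 0.32 SD at 10–14 (as in Table 1), 0.21–0.23 SD at 15–24, and 0.37–0.40 SD for the interaction. Table 1 gives neither of the last two, and its 0.17 does not apply to an age-specific claim. These values rest on two-sided tests, unit SD, no gain from covariate adjustment, and h between 6 and 27. The value of h is inferred, because the article does not state it.

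**What to change.** In the Data analysis section:

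1. Keep the two contrasts with control.
2. For the primary outcome, add an arm-by-age-group interaction (10–14 versus 15–24) to the adjusted model. Report comic minus flyer with its confidence interval and p-value within 10–14 and within 15–24.
3. Report the interaction test. The pooled comic-minus-flyer contrast can be shown alongside but should not stand in for the age-specific ones.
4. Count these contrasts in the multiplicity family and state the resulting value of h.
5. Add the MDEs for 15–24 and for the interaction to Table 1, and say which arms its rows compare.

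The cost is a few more contrasts and a slightly smaller alpha. For scale, raising h from 6 to 9 moves the pooled MDE from 0.172 to 0.177. No participants or measurements are added. The main limitation to accept openly is that the interaction has the least power of these tests.

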## Sample size and power considerations

To estimate the sample size and conduct the power analysis, we used the *R* package “Pwr” and the statistical software *G*Power* [26]. We calculated the minimum detectable effect size (MDE) for primary and secondary outcomes, which represents the smallest effect size that would be sufficient to detect statistical significance, based on a predetermined level of significance (*α*), sample size (*N*), and statistical power (1—*β*). We began by computing the power for t-tests of means to achieve a target power of 0.80. This process was conducted separately for each of the two waves in our study, which include three treatment arms and three age subgroups. In our calculations, we used the guideline* α* = 1 − (1 − 0.05) ^(1/√*h*) [27], where *h* was computed based on the number of treatment arms and outcomes. The overall sample size was set at *N* = 2007. For Wave 1, we allocated the sample size as N/3 per treatment arm. Anticipating a 10% attrition rate for follow-up measurements in Wave 2, the adjusted sample size was calculated as *N* = *n* = (sample/3) * (1—attrition). For the subgroup analysis in Wave 1, the sample size per age subgroup was assumed as *N* = sample/9, (i.e., N divided by 3 treatments arms * 3 age subgroups). Similarly, the adjusted sample size for Wave 2 subgroup analysis, the adjusted sample size was *n* = (sample/9) * (1—attrition). We used *R* Power to input the calculated MDEs and illustrate how each subgroup sample size corresponds to power levels (See Table 1).

**Table 1 Tab1:** Required sample size and minimum detectable effect size (MDE) for each wave and full and subgroups

Sample	Treatment (N)	Comparison (N)	Cohen’s *d* Wave 1	Cohen’s *d* Wave 2
Full treatment (Comic book, Flyer, Control)	669	669	0.17	0.18
Age sub-groups	223	223	0.32	0.34

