**Fig. 1 Fig1:**
[figure not shown]
Trial flow chart

As part of the DASH cohort study, which this trial is nested, all participants will take part in a survey interview of approximately 60–90 min. Each interview will begin with the data collector providing the consent form. If the participant consents, they will be asked survey questions regarding mental health literacy, anxiety, and depression before the intervention is administered, which will serve as baseline measures. For participants assigned to the comic book intervention, the data collector will provide the printed comic book to the participants, reading the text aloud. For participants assigned to the flyer intervention, the process will be the same where the data collector will provide the printed flyer, reading the text out loud. Participants in the control group will be provided with no additional instructions or interventions. Participants will then be asked other survey questions regarding sexual and reproductive health providing a brief break between the intervention implementation and the post-intervention survey. All participants will be surveyed on mental health literacy, anxiety, depression, and intentions to cope as a post measure.

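### The primary model for mental health literacy adjusts for intentions to cope, a secondary outcome measured only after the intervention, so the arm coefficient need not be the total randomised effect

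*Protocol article*

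**What the plan says.** The Data analysis section of the protocol article defines the primary model: MHL after the intervention is regressed on the three arms, dummy-coded against control. On baseline adjustment it says "We will control for baseline MHL scores by including them as a covariate". It then adds that "covariates such as depressive and anxiety symptoms, intentions to cope, age, gender, and education levels will be included in the model". Later in the same section, each secondary outcome is regressed on trial arm in its own linear model.

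Two other sections fix when coping is measured:

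- **Procedure, before the intervention:** participants who consent are interviewed, and "they will be asked survey questions regarding mental health literacy, anxiety, and depression before the intervention is administered, which will serve as baseline measures". Coping is not in this list.
- **Procedure, after the intervention:** "All participants will be surveyed on mental health literacy, anxiety, depression, and intentions to cope as a post measure". Coping appears here for the first time.
- **Outcome measures:** the secondary outcomes are the PHQ-2, the GAD-2 "and the 2-item Intentions to Cope scale [34], all measured post-intervention". The primary scale, by contrast, is described as taken both before and after.

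The Introduction says of the comic and flyer that the material "describes the mental disorders of anxiety and depression as well as information around help-seeking and coping".

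**The concern.** As described, the plan has no pre-intervention coping score, so the coping covariate in the primary model can only be the post-intervention one. The same variable is then used as a possible effect of the arm (secondary analysis) and as something held fixed when the arm effect on MHL is estimated (primary analysis).

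Randomisation balances what precedes allocation, not what follows it. Holding a post-intervention variable fixed removes whatever part of the MHL effect runs through coping. If coping and MHL also share unmeasured causes, it adds a non-causal component. The hypotheses concern the whole effect of receiving the comic or flyer, and this coefficient need not estimate that. The planned variance inflation check looks for collinearity among predictors and would not reveal the problem.

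**Working it through.** **Inputs from the protocol article (Sample size and power considerations).** N = 2,007, and "For Wave 1, we allocated the sample size as N/3 per treatment arm", so n = 669 per arm. Target power is 0.80, attrition at Wave 2 is 10%, and the minimum detectable d for full arms is 0.17 (Wave 1) and 0.18 (Wave 2). Alpha = 1 − 0.95^(1/√h), with h not stated.

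**Reproducing the plan's figure.** I solved a two-sided two-sample t-test for d at 80% power, with n = 669 and n = 669 × 0.9 = 602.1:

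| h | alpha | d, Wave 1 | d, Wave 2 |
|---|---|---|---|
| 3 | 0.0292 | 0.165 | 0.174 |
| 4 | 0.0253 | 0.169 | 0.178 |
| 6 | 0.0207 | 0.173 | 0.182 |
| 7 | 0.0192 | 0.174 | 0.184 |
| 8 | 0.0180 | 0.176 | 0.185 |

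Both printed values (0.17 and 0.18) are reproduced for h = 4 to 7, that is, for alpha from about 0.019 to 0.025. This range is inferred.

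**Assumptions (not in the documents).** Outcomes are scaled to residual SD 1. dC is the arm effect on coping in SD units. r is the within-arm correlation of coping with post-intervention MHL, given the other covariates. I take dC from 0 to 0.3 and r from 0.1 to 0.5.

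**Formulas.**
- Expected arm coefficient with coping in the model = d − r × dC.
- Its standard error ≈ √(1 − r²) × √(2/669) = √(1 − r²) × 0.0547.

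A regression simulation (600 replicates, 669 per arm, true effect 0.17, dC = 0.2, r = 0.25) gave a mean of 0.168 without coping and 0.119 with it. The formula gives 0.17 − 0.25 × 0.2 = 0.120.

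**True d = 0.17.** Power is shown for alpha 0.019 to 0.025:

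| dC | r | Expected estimate | Attenuation | Power |
|---|---|---|---|---|
| coping not in model | – | 0.170 | 0% | 78–81% |
| 0 | 0.3 | 0.170 | 0% | 82–85% |
| 0.1 | 0.1 | 0.17 − 0.01 = 0.160 | 6% | 73–76% |
| 0.17 | 0.3 | 0.17 − 0.051 = 0.119 | 30% | 48–52% |
| 0.17 | 0.5 | 0.17 − 0.085 = 0.085 | 50% | 29–33% |

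**No true MHL effect.** The coefficient centres on −r × dC, so any excess rejections point the wrong way:

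| dC | r | Shift | Shift / SE | Rejection, two-sided 5% |
|---|---|---|---|---|
| 0.1 | 0.1 | −0.01 | −0.18 | 5% |
| 0.3 | 0.3 | −0.09 | −1.73 | 41% |
| 0.3 | 0.5 | −0.15 | −3.17 | 89% |

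At the inferred alpha of 0.019, the last two figures are 27% and 80%.

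**The case against.** **Bias is not certain.** A reader might infer that the primary estimate will be biased. The documents do not support that. The shift is a product of two unknowns and vanishes if either is zero. In that case the covariate does no harm and may even add precision (second row of the first results table). The Introduction mentions coping content, but the fuller description of the two comic pages under Interventions does not list it, and the Discussion stresses that the exposure is light-touch. A small or null effect on coping is therefore possible. This limits the claim to what can happen. It does not rescue the model, because validity would then depend on one of the trial's own secondary hypotheses being null.

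**The larger figures rest on strong assumptions.** A coping effect of 0.3 SD with no MHL effect is nearly twice the detectable difference and has no source. The mildest case shown costs 6% of the effect and leaves false rejection near 5%.

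**An unlisted baseline coping item could exist.** Fig. 1 and the survey instrument are not visible, and the covariate list is given by way of example. But the Procedure names the measures at both time points and adds coping only at the second. If a baseline item exists, the text has to say so.

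**Covariate detail belongs in the SAP.** That would answer an omission. Here the article names the covariate and commits to including it.

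**Two wider readings do not stand.** A reader might infer that depression and anxiety also enter as post-intervention scores. The Procedure says their pre-intervention scores serve as baseline, which is the natural reading, so only the time point needs stating. A reader might also extend the defect to the secondary models, but the article names no covariates for those.

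**Conclusion.** The point holds for one covariate in one model. As written, the primary MHL regression conditions on a post-randomisation secondary outcome, so its arm coefficient is not in general the total randomised effect.

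The direction is most likely toward the null, provided the materials improve coping and coping correlates positively with MHL. Within the assumed ranges the consequence runs from nothing, through a 6% attenuation, to a halving of the effect with power near 30%. The documents give neither the coping effect nor the correlation, and the power figures use an inferred alpha because h is not stated. The defect itself does not depend on these numbers: it follows from the measurement schedule and the covariate list.

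**What to change.** Remove intentions to cope from the covariates of the primary MHL model and keep it as a secondary outcome. If its relation to MHL is of interest, use it only in a separate analysis labelled as mediation.

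As a clarification in the same sentence, state that the depressive and anxiety covariates are the pre-intervention PHQ-2 and GAD-2 scores.

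The cost is one line of analysis wording. Sample size, data collection and the other analyses are unaffected.
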